### Statistical Analysis

Descriptive statistics will be used to summarize the sample with regard to baseline characteristics of interest. Means and SDs will be presented for continuous variables, while sample proportions will be provided for categorical variables.

Primary assessment of intervention effects will be based on intent-to-treat analyses. As-treated effect parameters will be estimated in secondary, exploratory analyses. We will conduct intervention intensity-adjusted analyses (estimating the dose that participants received) by substituting a score between 0 and 1 for the treatment group. Additionally, we will conduct per-protocol analyses, with participants exposed to “intervention as intended” in the treatment arm and all others treated as controls (ie, 0). Generalized linear mixed models will be used to account for stratification by city, correlation between youth from the same neighborhood, as well as the correlation between longitudinal observations from the same youth. SAS (Statistical Analysis System) software (SAS Institute) will be used for all statistical analyses. All hypotheses will be 2-sided tests with a significance level of 5%, and 95% CIs will accompany all sample statistics.

Participation bias will be assessed by comparing the age and race or ethnicity of youth participating in the study to each neighborhood’s overall demographics of youth (based on census tract data). Attrition analysis will be conducted by comparing youth who completed follow-up surveys with those who did not, based on demographics as well as outcomes measured at baseline. Mechanisms for missing data will be investigated by comparing important covariates between youth with and without missing data at each time point. We will characterize these mechanisms as (1) missing completely at random, (2) missing at random, or (3) not missing at random. If the nature of our missing data is ignorable (either missing completely at random or missing at random), we will use imputation methods, such as multiple imputation via chained equations, to handle dropout. Ultimately, sensitivity analyses will be conducted to compare the results of our imputation methods to complete-case and available-data analyses.

Exploratory mediation of intervention effects will be tested using methods such as structural equation modeling, and moderation will be examined using methods such as latent class analysis. Preplanned subgroup analyses will explore heterogeneity by sex, prior violence exposure, and neighborhood context.

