### Randomization and Allocation Concealment

Th*e* trial design builds on primary prevention principles that emphasize a comprehensive, theory-driven approach, sufficient dosage (through repeated exposure to content), and youth participation balanced with the feasibility and cost of implementation approaches. Randomization is performed at the neighborhood level (ie, cluster) to reduce the risk of contamination. Neighborhoods are stratified by city (Pittsburgh vs Washington, DC, and Maryland metro areas [DMV]) and randomized 1:1 to FHF or enhanced usual care (wellness check-ins) by the study statistician using reproducible code. Randomization lists are generated prior to enrollment and implemented centrally; site teams will be notified of the assignment after cluster confirmation. Analyses will be conducted with masked arm labels, and outcome assessments will use standardized instruments to minimize bias.

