### Sample Size and Power

In determining the number of neighborhood clusters to include in the study, we sought to balance expected effect sizes with feasibility and budgetary constraints for a 3-year multicity study. Our selection of 16 clusters was informed by a previous cluster-RCT led by our team to evaluate the Manhood 2.0 curriculum and a pilot feasibility study of the Sisterhood 2.0 program (NCT02427061 and NCT04388696, respectively). We used these study findings to guide assumptions for our sample size calculations [34,39,40,46]. Sample sizes for each outcome were based on clinically meaningful differences between treatment groups with respect to changes in outcomes across time (ie, intervention effect). For the primary outcome of self-reported youth violence perpetration (fighting or weapon violence perpetration) in objective 1, the necessary sample size was calculated based on traditional methods that assume a fixed number of clusters. If we assume 8 neighborhoods randomized per arm with a conservative within-site correlation of 0.01, and 20% attrition at 3 months, we need 360 participants per arm (total N=720) to detect a standardized effect size of 0.39 with 80% power. This translates to a 35% relative reduction in the primary outcome, assuming a 57% rate in the control arm at 3 months. For all secondary outcomes, we have similar power to detect a standardized effect size of 0.39.

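### The exploratory per-protocol and dose analyses recode the randomized arm by exposure received, so randomization does not protect them, and per-protocol is a misleading name for the first

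*Protocol article*

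**What the plan says.** Four statements in the protocol article matter here.

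- Statistical Analysis, primary: "Primary assessment of intervention effects will be based on intent-to-treat analyses".
- The next sentence sets the status of what follows: "As-treated effect parameters will be estimated in secondary, exploratory analyses".
- The dose analysis is carried out "by substituting a score between 0 and 1 for the treatment group".
- The analysis named per-protocol takes as exposed the participants who had the intended intervention "in the treatment arm and all others treated as controls (ie, 0".

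Under Randomization and Allocation Concealment, the unit is the neighborhood: "Randomization is performed at the neighborhood level (ie, cluster) to reduce the risk of contamination". The Abstract says that the primary models adjust for baseline values and city. The article does not say whether the exploratory models do the same. For the exposure analyses it names no adjustment for predictors of attendance and no use of assignment as an instrument. It gives no expected attendance. The threshold for intended exposure is not defined here, which may be left to the SAP and is not part of this point.

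**The concern.** A per-protocol analysis usually drops participants who did not adhere. Here, FHF-assigned youth who fell short are kept and coded 0 together with youth from comparison neighborhoods. Treatment then varies inside each FHF neighborhood, and part of the estimate compares youth who attended with neighbors who did not. The dose analysis has the same weakness, because its 0-to-1 score is set by what each youth chose or was able to attend.

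The program is 12 sessions of about two hours, and participation is voluntary. Youth who stop attending may well differ in violence risk from those who stay. If they do, both estimates mix that difference with the effect of the program.

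These are the only estimates of the effect of receiving FHF that the article describes, and its two-sided 5% testing rule covers all hypotheses. A per-protocol result or dose gradient published beside a null intention-to-treat result could be read as evidence that FHF works when received.

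**Working it through.** **The plan's own figure.** There is none for these analyses. The sample-size statement concerns the main comparison. From it come 360 × 0.8 = 288 evaluable youth per arm, or 45 × 0.8 = 36 in each of 16 neighborhoods, and an intracluster correlation of 0.01.

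**Assumed inputs.** Let *f* be the share of FHF youth with the intended exposure, and *g* the amount by which non-adherers exceed adherers in violence, in SD. Neither is in the article, so ranges are shown.

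**Bias with no true effect, unadjusted.** Set the mean of each randomized arm to 0.

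- FHF adherers: −(1−f)g
- FHF non-adherers: +f·g
- Pooled group coded 0: 288(1−f)·f·g / [288 + 288(1−f)] = f(1−f)g/(2−f)
- Contrast: −(1−f)g − f(1−f)g/(2−f) = **−2(1−f)g/(2−f)**

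| f | g | Contrast (SD) |
|---|---|---|
| 0.8 | 0.2 | −2(0.2)(0.2)/1.2 = −0.067 |
| 0.6 | 0.3 | −2(0.4)(0.3)/1.4 = −0.171 |
| 0.5 | 0.5 | −2(0.5)(0.5)/1.5 = −0.333 |
| 0.4 | 0.5 | −2(0.6)(0.5)/1.6 = −0.375 |
| any | 0 | 0 |
| 0.6 | −0.3 | +0.171 |

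The same formula holds for a rate. With the article's 57% control rate, f of 0.5 to 0.8 and a gap of 10 to 20 percentage points, the false risk difference is −0.033 to −0.133 (apparent relative risk 0.94 to 0.78). With the gap reversed (−10 points) it is +0.033 to +0.067.

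**Simulation under the planned kind of model.** There were 16 neighborhoods of 36 youth, intracluster correlation 0.01, city in the model, no true effect, and 1,000 runs per setting. Assumptions: adherence 50% or 70%, baseline/follow-up correlation 0.5, and a dose between 0 and 0.5 (mean 0.25) for non-adherers. Selection is the correlation between the propensity to adhere and lower latent risk.

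| Selection | Analysis | Unadjusted bias (SD); false positives | Baseline-adjusted bias (SD); false positives |
|---|---|---|---|
| 0.2 to 0.5 | Per-protocol | −0.12 to −0.42; 26-99% | −0.07 to −0.21; 13-66% |
| 0.2 to 0.5 | Dose | −0.10 to −0.36; 17-93% | −0.06 to −0.18; 11-48% |
| 0 | Both | about 0; 4-5% | about 0; 4-6% |
| −0.3 | Per-protocol | +0.19 to +0.25; 52-71% | +0.10 to +0.12; 22-29% |
| any | Intention-to-treat | about 0; 4-6% | about 0; 5-8% |

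Adjusting for baseline removes about half of the bias in each setting.

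**With a real effect.** Take a full-dose effect of −0.39 SD, proportional to dose, 60% adherence and no selection. The per-protocol coding should give about −0.39 + (0.4 × 0.25 × 0.39)/1.4 = −0.36, and the simulation gave −0.35. The effect is diluted because partly treated youth sit among the controls. The dose analysis recovers −0.39. With selection of 0.3 and baseline adjustment, the two give −0.46 and −0.49.

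**An estimate that uses assignment.** In those two settings the intention-to-treat estimates were −0.275 and −0.273. Mean dose in the FHF arm is 0.6 + 0.4 × 0.25 = 0.70. The ratios are −0.275/0.70 = −0.39 and −0.273/0.70 = −0.39, correct with or without selection. Dividing by the 60% adherence share instead gives −0.275/0.60 = −0.46, too large, because partial attendance also had an effect.

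**The case against.** The strongest reply is that the protocol has already put these analyses in their place. Intention-to-treat is primary, and the dose and per-protocol analyses follow directly on a sentence calling such estimates as-treated, secondary and exploratory. That stands, and it limits the damage. What remains is that one of them carries the name per-protocol while its coding is as-treated, and that no receipt estimate using the randomized arm is described.

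A reader might infer that the recoding produces an apparent benefit even if FHF does nothing. The document does not support that. The coding alone gives no bias; a false benefit needs lower-risk youth to attend more. That is plausible, but the article reports neither attendance nor its relation to risk, and the opposite selection would give a false harm.

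It can also be said that baseline adjustment would help. It would, by about half under the assumed correlation, if it is applied to these models, which the article does not state.

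Finally, an instrumental estimate has assumptions of its own. Assignment must act only through the measured exposure, a binary adherence version fails if partial attendance helps, and inference on 16 clusters is fragile. All of this stands. It bears on how the alternative is specified, and it does not justify placing FHF youth among the controls.

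**Conclusion.** The point holds for the two exploratory exposure analyses. Both are as-treated contrasts without the protection of randomization, and per-protocol is the wrong name for the first. The primary intention-to-treat conclusion is untouched.

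The direction of bias cannot be known from the article. With no true effect, 40-80% adherence and adherers lower in violence by 0.2-0.5 SD, the unadjusted per-protocol contrast lies between −0.07 and −0.38 SD; the upper end is close to the trial's 0.39 target. It is zero with no gap and positive with the opposite gap. Baseline adjustment roughly halves it if the baseline/follow-up correlation is about 0.5. With a real effect and no selection, the per-protocol coding dilutes the effect. The loss of randomization is certain from the text; the sizes rest on assumed adherence, gap and correlation.

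**What to change.** 1. Do not recode FHF-assigned youth as controls.
2. Estimate the effect of receipt with randomized neighborhood assignment as the instrument for dose (sessions attended), adjusted for city and baseline value, with inference suited to 16 clusters.
3. If a binary-adherence version is also reported, state its assumption that partial attendance has no effect.
4. If the as-treated contrasts are kept, rename the per-protocol one as as-treated and report both as non-randomized.

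The cost is a wider interval for the effect of receipt, reliance on the assumption that assignment works only through attendance, and a little more programming. Session attendance is already a planned metric, and the planned dose analysis already needs it linked to the survey data, so no new data are required.

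### Imputation is made to depend on a MAR versus not-MAR label that observed covariates cannot supply, and the named sensitivity analyses do not probe outcome-dependent dropout

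*Protocol article*

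**What the plan says.** The Statistical Analysis section of the protocol article sets out a sequence.

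- Evidence: "Mechanisms for missing data will be investigated by comparing important covariates between youth with and without missing data at each time point". A separate attrition analysis compares youth who did and did not complete follow-up, "based on demographics as well as outcomes measured at baseline".
- Label: "We will characterize these mechanisms as (1) missing completely at random, (2) missing at random, or (3) not missing at random".
- Action: "If the nature of our missing data is ignorable (either missing completely at random or missing at random), we will use imputation methods", with chained equations given as an example.
- Sensitivity: "sensitivity analyses will be conducted to compare the results of our imputation methods to complete-case and available-data analyses".

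No action is attached to the third label. The Sample Size and Power section assumes "20% attrition at 3 months, we need 360 participants per arm (total N=720) to detect a standardized effect size of 0.39 with 80% power" and adds: "This translates to a 35% relative reduction in the primary outcome, assuming a 57% rate in the control arm at 3 months".

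**The concern.** The choice of method for missing primary-outcome data hangs on a diagnosis that the planned evidence cannot deliver. MAR and not-MAR differ only in how missingness relates to values that were not recorded, once the recorded data are taken into account. Baseline covariates, demographics and baseline outcomes are all recorded data. They can show that missingness is not completely at random and can say nothing further. Whoever applies the rule must therefore make a judgement after seeing the data, and one of the three possible answers leads to no stated analysis.

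The named sensitivity analyses do not close the gap. Multiple imputation as described, and a mixed model on available data, rest on MAR. Complete-case analysis needs MCAR, or missingness that depends only on modelled covariates. Agreement among the three gives no reassurance about dropout driven by the outcome itself.

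That kind of dropout is plausible here. The primary outcome is self-reported fighting and weapon violence, and youth involved in violence may be harder to reach. Attrition is named as a risk under Expected Findings. Programme contact also differs between arms, so the pattern of loss might too.

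**Working it through.** **Step 1. The plan's own figures.** From Sample Size and Power: control rate 57%, relative reduction 35%, attrition 20%, standardized effect 0.39.

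- FHF rate: 0.57 × 0.65 = 0.3705. Planned difference: 0.57 − 0.3705 = 0.1995.
- Mean rate: (0.57 + 0.3705)/2 = 0.47025. Standardized: 0.1995/√(0.47025 × 0.52975) = 0.40, close to the stated 0.39.

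**Step 2. Can the covariate comparison separate MAR from not-MAR?** Take a binary baseline risk factor x with prevalence 0.5 and build two settings. All inputs in this step are assumptions, chosen to give about 20% missing.

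- Setting A (not-MAR): the outcome rate is 0.25 if x = 0 and 0.50 if x = 1. Dropout is 0.32 for violent youth and 0.13 for the others, whatever x is.
  - Missing given x = 0: 0.25 × 0.32 + 0.75 × 0.13 = 0.1775.
  - Missing given x = 1: 0.50 × 0.32 + 0.50 × 0.13 = 0.225.
  - Outcome rate among the observed, x = 0: 0.25 × 0.68/0.8225 = 0.207. For x = 1: 0.50 × 0.68/0.775 = 0.439.
- Setting B (MAR): the outcome rate is 0.207 if x = 0 and 0.439 if x = 1. Dropout depends on x only, at 0.1775 and 0.225.

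| Quantity | A (not-MAR) | B (MAR) |
|---|---|---|
| Missing | 20.1% | 20.1% |
| x = 1 among missing, 0.225/(0.1775 + 0.225) | 55.9% | 55.9% |
| x = 1 among observed, 0.775/(0.8225 + 0.775) | 48.5% | 48.5% |
| Observed outcome rate, x = 0 / x = 1 | 0.207 / 0.439 | 0.207 / 0.439 |
| Rate after MAR imputation, (0.207 + 0.439)/2 | 32.3% | 32.3% |
| Completers only, (0.17 + 0.34)/(0.8225 + 0.775) | 31.9% | 31.9% |
| True rate | 37.5% | 32.3% |

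A simulation of 2,000,000 records per setting gave the same values to within 0.1 percentage point. Everything the plan would look at is identical in A and B, so no covariate comparison can tell them apart. In A, imputation (32.3%) and complete cases (31.9%) nearly agree, and both miss the true 37.5% by more than 5 points. This is one group only. The same mechanism acting in both arms would partly cancel in the treatment comparison.

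**Step 3. What could it do to the treatment effect?** Let a be the attrition in an arm, p the true rate, r the rate among completers, and δ the excess of dropouts over completers that remains after baseline adjustment. Then p = (1 − a)r + a(r + δ), so r = p − aδ. With the same δ in both arms, the control-minus-FHF difference is shifted by (a_FHF − a_control) × δ. The gaps and excesses below are assumptions.

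- Gap of 10 points, δ = 0.30: 0.10 × 0.30 = 0.030, and 0.030/0.1995 = 15% of the planned difference.
- Gap of 15 points, δ = 0.30: 0.15 × 0.30 = 0.045, and 0.045/0.1995 = 23%.
- Equal 20% loss, δ larger by 0.30 in one arm: 0.20 × 0.30 = 0.060, and 0.060/0.1995 = 30%.

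On the standardized scale, with 20% loss and dropouts shifted in one arm only, a shift of 0.25, 0.5 or 1.0 SD gives a bias of 0.05, 0.10 or 0.20 SD. Divided by 0.39, that is 13%, 26% or 51% of the design effect.

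The direction depends on which arm loses more youth, or has the larger excess among its dropouts.

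**The case against.** **The article is condensed.** A delta-adjusted or tipping-point analysis is the sort of detail an SAP carries, and the article does not say that its sensitivity analyses are the only ones. This stands. A reader might infer that the trial has no analysis for informative dropout, but with the SAP not shown the documents do not support that. The objection does not rescue the classification rule, which is written out in the article and cannot be carried out as written.

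**Attrition by arm.** A reader might infer that attrition will be examined only overall. The text is silent on arm, and the Results section plans a CONSORT flow, which conventionally shows losses by arm.

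**Contact by arm.** It is tempting to set 12 sessions against a single 20-minute check-in. The description of the comparison arm also offers optional follow-up and further phone check-ins, and the retention measures and survey payments are described without distinction by arm. Differential loss remains possible but is not shown.

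**Size.** The documents give one attrition figure, 20%, and nothing on a gap between arms or an excess among dropouts. With equal attrition and equal excess the shift is zero. Baseline adjustment removes part of any raw excess, so only the remainder counts. The rate scale is also not that of the primary outcome, which is a score from 0 to 21. At the design effect the conclusion would survive. There are 360 × 0.8 = 288 youth per arm, or 36 per neighborhood, and the design effect is 1 + 35 × 0.01 = 1.35, so the effective number is 288/1.35 = 213 per arm. The standard error is √[(0.57 × 0.43 + 0.3705 × 0.6295)/213] = 0.047. An attenuation of 4.5 points leaves 0.1545/0.047, about 3.3 standard errors. All of this stands. A bias away from the null would matter more if the true effect were small: 0.045 is close to one standard error.

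**Conclusion.** The point holds in two parts of different strength.

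1. The rule is wrong as stated. A comparison of observed covariates can count against MCAR but cannot separate MAR from not-MAR. Imputation should not depend on that label, and the not-MAR label has no stated consequence. This rests on no numerical assumption.
2. The sensitivity analyses named in the article do not address dropout that depends on the unobserved outcome given the observed data. They could agree and share a bias. It would go too far to say that they will. Bias in the treatment effect requires dropout to depend on the outcome beyond the baseline data, and to do so unequally between arms through the amount of loss, the excess among dropouts, or both.

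The shift of 3 to 4.5 points, or 15% to 23% of the planned difference, is an illustration and not an estimate. Only the 20%, 57%, 35% and 0.39 come from the article.

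**What to change.** - Remove the three-way classification as a condition for the method. Keep the covariate comparison to assess MCAR and to choose auxiliary variables for the imputation model.
- State MAR, given the baseline outcome and the listed covariates, as the working assumption of the primary analysis, whatever that comparison shows.
- Add, or confirm in the SAP, a prespecified delta-adjusted or tipping-point analysis on the 0 to 21 score. Shift the imputed values for dropouts separately by arm, including a shift in one arm only, over a range fixed before arm labels are unmasked. Report the shift at which the conclusion changes. Imputed values should respect the bounds of the score.
- Confirm that the CONSORT flow gives losses by arm at each time point.

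The cost is a change of wording and modest extra analysis, with no new data. The article expects follow-up to run to July 30, 2026 and analysis of the primary end points on January 1, 2027, so the change can be fixed before outcomes are analyzed.

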### Ethical Considerations

The protocol for this study has been approved by the University of Pittsburgh Institutional Review Board and has been registered on ClinicalTrials.gov (NCT05743478). Procedures prioritize confidentiality and minimize risk: surveys are anonymous; distress protocols include on-site support, warm handoffs to behavioral health services, and mandatory reporting limited to legally required circumstances. Parental permission waivers and oral assent procedures for youth will be used where justified to reduce participation barriers. All staff are trained in trauma-informed, youth-centered practices. During the recruitment process, all potentially eligible youth will be reminded that participation is completely voluntary and that whether or not they participate will have no effect on their participation in any of the organization’s programs and activities. Participants can choose not to answer any questions or discuss any topics that make them uncomfortable. All data collection materials will be anonymous and will contain no personal identifying information. Data are further protected by a Certificate of Confidentiality from the Centers for Disease Control and Prevention (CDC). Following surveys and interviews, we will briefly check in with each participant to assess for emotional distress. Should a participant display signs of emotional distress or disclose to the research assistant that they are in danger of hurting themselves, hurting others, or being hurt, the research assistant will follow an established protocol to notify appropriate community agency personnel and ensure that the participant receives urgent evaluation. Additionally, a systematic review of notes from research assistants will be conducted to ensure that participants experiencing distress are being connected directly with the community site leads or administrators, receiving educational materials, and being referred appropriately; this includes ensuring that all research assistants document asking each participant about emotional distress after completion of the survey and interview and giving all participants a set of resources to take with them after completing the survey. If we learn that a participant is in danger of hurting themselves, hurting others, or being hurt, we will inform the appropriate authorities (eg, Children, Youth, and Families), as we are required to do under Pennsylvania law. Youth will receive US $20 for completing the baseline survey, US $30 for the end-of-program survey, US $30 for the 3-month follow-up survey, US $50 for the 6-month follow-up survey, and US $30 for participating in a semistructured interview.

A data safety plan documents adverse event monitoring and reporting. Given the sensitivity of the questions being asked regarding violence perpetration, we also established an internal data safety and monitoring plan. The senior research coordinator is responsible for daily monitoring of data and safety. They work with research assistants to ensure that all data are collected and stored securely. The research team, consisting of the principal investigator ([name]), research coordinator, research assistants, data analysts, and other research staff as appropriate, meets weekly to review study progress, the status of data collection, and the safety of participants. Concerns will be reported to the institutional review board in accordance with institutional and CDC requirements.

